### Nurse mentors

Nurse mentors volunteer or were chosen by team leaders as those nurses with a special interest in and/or skills in family violence practice. They provide support to individual nurses in the team struggling with difficult cases or wanting to practice their IPV inquiry skills. They act as a ‘practice champion’ in the team.

The role of these nurses includes:

• Liaising with the family violence liaison officers in community-based family violence services

• Accompanying MCHNs who are undertaking a home visit for additional safety where there is or is likely to be IPV

• Facilitating and maintaining discussions within the team about IPV issues

• Acting as a secondary referral, debriefing and support person for nurses managing difficult cases of IPV

### Family violence MCHN liaison workers

MOVE adopted the model outlined in the IRIS study [20] of a family violence agency staff member who has a special responsibility for liaison with primary care services; in this case, with the MCH nurse teams to strengthen links and referral options. These staff are funded, employed and managed by the family violence services, with agreed responsibility during the trial for:

• Attending MCHN team meetings to familiarize the team with the FV service and other relevant community-based services, e.g. community police

• Facilitating referrals and secondary referrals to family violence services

• Providing feedback about referrals, debriefing if necessary

• Participating in evaluation interviews

The geographical location of the two family violence services resulted in one family violence liaison worker liaising with one team and the other liaising with three teams.

### Implementation

Following all stakeholders’ agreement with the new model, nursing consultants and MOVE staff briefed the intervention teams and provided them all with newly developed resources (http://www.latrobe.edu.au/mchr/html/move.html) including a guide to IPV documentation. Teams undertook to implement the MOVE model over a twelve month period. During the intervention period, MOVE research staff remained at a distance to enhance sustainability, and reliance on research staff was kept to a minimum.

### Data collection

*Process evaluation*: Online survey questions for nurses, structured using tenets of the Normalization Process Theory [36] were developed in consultation with nurse consultants, face validity was checked with assessment by stakeholders in the reference group and they were then piloted with an MCH nurse team outside the trial to ensure acceptability, relevance and timeliness.

The online survey was developed for use six months into the implementation year with all participating nurses in both arms to elicit MCHN current IPV screening knowledge, attitudes and work practices.

At the same time, telephone or face-to-face interviews were planned with MCH nurse mentors, team leaders, family violence liaison officers and supervising staff from family violence agencies to elicit factors related to key concepts of the NPT framework. Interviews were conducted by external staff.

#### *Impact evaluation* - o*nline survey data*

Three months after the end of the intervention, a second anonymous online survey of MCH nurses in both arms of the study (~160) was developed to assess their levels of confidence about and attitudes to IPV screening, perceived rates of inquiry about women’s and children’s safety, referral to family violence agencies for all family members, team functioning and support for IPV screening and perceptions of their own safety. The surveys and interviews will be repeated two years after the end of the intervention to assess sustainability of the screening processes. Interviews conducted by external staff with key stakeholders will also be conducted at the end of the intervention and two years later.

#### Outcome evaluation - primary and secondary outcomes

##### Routine data

With local government permission, we will retrieve routine data about family violence described above for the intervention period for all nurses in both arms of the study. We will seek to retrieve it again in 2013, two years post intervention.

##### Women’s survey questionnaire

We have developed a questionnaire survey to be sent to 10,000 women (5000 in either arm) who have given birth over an eight month period. This sample gives us power to detect differences in the primary outcome. Included are all the primary and secondary outcome measures and a valid and reliable measure of intimate partner violence (Composite Abuse Scale) [29].

The data management company employed to manage the survey data has been subcontracted to the local government councils who have given the company staff access to women client’s addresses. They will mail the surveys and two rounds of reminder cards. Surveys will be returned to the company for electronic data entry and double-coding.

##### Checklists (http://www.latrobe.edu.au/mchr/html/move.html)

MOVE staff will retrieve all checklists retained by intervention nurses at intervention midpoint (six months) and after the implementation period has finished. Data will be checked for completion of screen and screening period.

### Data analysis and reporting

#### Women’s survey

The MCH consumer survey data will be cleaned, double-coded and entered into a secure database by an external company blinded to the study arms. It will then be forwarded to a statistician blinded to study arm. Women’s characteristics for socio-demographic and birth characteristics will be compared by trial arm to ensure that randomization was effective. The representativeness of the women responding to the survey (i.e. sample bias due to differential study participation rates) will be assessed by comparison with routine perinatal data for all women giving birth in the region for the comparison year (Victorian Perinatal Data Collection Unit, DHS).

All data will be analyzed by intention-to-treat and variance estimates in models will be adjusted for the effect of the clustered (LGA) selection of participants. We will analyze data using contingency table analyses for bivariate and binary logistic regression with robust standard errors for multivariate models. For primary outcomes, we will analyze data stratified by and adjusted for women’s abuse status and for potentially significant confounding variables (where randomization is less effective in removing bias across study groups), including women’s socio-economic status.

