### Aims

1) To compare whether, after implementing an evidence-based consensus model of good IPV practice for twelve months, MCH nurses in the intervention arm more frequently than nurses in the comparison arm

• Ask about IPV among their client population

• Refer women experiencing IPV to services

• Inquire about the safety of women and children in the relationship

2) More women attending MCH centres in the intervention arm than in the comparison arm:

• Are asked about IPV

• Disclose/discuss any abuse and

• Are satisfied with the quality of care and support they receive

3) To provide an accurate estimate of the proportion of MCH clients who have ever or who are currently experiencing IPV and those abused when pregnant

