### Secondary outcomes are to

1. Estimate the prevalence of any IPV in the previous 12 months (measured with the Composite Abuse Scale, ≥3-6, and ≥7), IPV during pregnancy and any reported child abuse

2. Increase the proportion of MCH clients reporting satisfaction with quality of care and support they receive for themselves, their partners and their children

3. Investigate the proportions of women reporting any harm arising from (a) responding to questions about IPV in their MCHN consultation or (b) responding to questions about IPV in the survey)

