#### Survey sample size calculation

(b) We calculated that around 8-10% of women attending each of the eight MCH services will have been abused in the previous 12 months [4]. Following twelve months implementation, we will send a mailed questionnaire to all women who have given birth in the previous 8 months in both the comparison and intervention municipalities (5000 per arm). This sample size enables us to detect a predicted increase of 15% average disclosure found previously in a screening intervention of screening vs usual care [27]. We have taken into account both the numbers of births in participating local government areas (using most recent published data (2005), the likely response fraction (55-65% following mailed surveys and a reminder postcard - a modified Dillman procedure) and also adjusted for clustering. We adjusted for an intra-cluster correlation of 0.02 from a previous IPV primary care study [28].

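### Aim 3 promises an accurate IPV prevalence although 35–45% of women are expected not to respond, and the only stated safeguard is a descriptive comparison with regional perinatal data

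*Protocol article*

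**What the plan says.** The Aims section of the protocol article includes: "To provide an accurate estimate of the proportion of MCH clients who have ever or who are currently experiencing IPV". The secondary outcomes repeat this as "Estimate the prevalence of any IPV in the previous 12 months", using two cut-offs of the Composite Abuse Scale.

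The survey goes to 10,000 women, 5000 per arm. The Survey sample size calculation section allows for "the likely response fraction (55-65% following mailed surveys and a reminder postcard".

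The Women's survey part of Data analysis and reporting then makes three relevant statements:

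- Socio-demographic and birth characteristics of survey women are compared by arm, with the stated purpose of checking that randomisation worked.
- Representativeness, meaning bias from differential participation, "will be assessed by comparison with routine perinatal data for all women giving birth in the region for the comparison year".
- Primary outcomes are stratified by and adjusted for abuse status, and adjusted for possible confounders including socio-economic status.

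The reporting list that follows gives the prevalence measures overall and by arm. Neither section says whether or how the perinatal comparison alters a prevalence figure.

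**The concern.** Between 35% and 45% of the women mailed are expected not to answer. Whether a woman returns a booklet sent to her home may well depend on whether she is being abused, or on circumstances linked to abuse. A comparison that only describes how responders differ from all women giving birth can reveal a problem, but it leaves the prevalence figure as it was. The adjustment that is stated is for primary outcomes and does not reach Aim 3.

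A second, smaller issue affects the trial comparison. The two checks are a comparison of responders between arms and a comparison of responders with the region. Neither, as described, sets each arm's responders against that arm's own births. At stake are the accuracy claimed for a main descriptive result of the study and the ability to interpret any imbalance between the arms' responders.

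**Working it through.** **Inputs from the article**

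- Surveys mailed: 10,000 (Women's survey questionnaire).
- Response fraction R: 55–65% (Survey sample size calculation).
- Prevalence: "around 8-10% of women attending each of the eight MCH services will have been abused in the previous 12 months". The 8–10% is used here as the observed responder prevalence p.
- Intra-cluster correlation 0.02 and eight teams. The correlation comes from an earlier primary care study of IPV; applying it to prevalence is an assumption.

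**Assumed input:** k, the ratio of prevalence in non-responders to that in responders, from 0.5 to 2. The article gives no value.

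**1. The plan's own figure.** The article states no precision for prevalence. The sample size is justified by disclosure ("This sample size enables us to detect a predicted increase of 15% average disclosure") without a baseline, significance level or power, so there is nothing to reproduce for Aim 3. The responder count follows directly: 10,000 × 0.55 = 5,500 to 10,000 × 0.65 = 6,500.

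**2. Sampling precision at the midpoint** (6,000 responders, p = 9%)

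- Ignoring clustering: 1.96 × √(0.09 × 0.91 / 6,000) = 0.72 points.
- Responders per team: 6,000 / 8 = 750. Design effect: 1 + 749 × 0.02 = 15.98, with square root 4.0.
- With clustering: 0.72 × 4.0 = 2.9 points.
- Over the stated ranges: 0.66–0.79 points ignoring clustering and 2.7–3.0 points with it.

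**3. Effect of non-response.** Overall prevalence = R·p + (1 − R)·k·p, so the shift from the observed figure is (1 − R)(k − 1)p.

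| k | R 55%, p 8% | R 55%, p 10% | R 65%, p 8% | R 65%, p 10% |
|---|---|---|---|---|
| 0.5 | 6.2% | 7.75% | 6.6% | 8.25% |
| 1.5 | 9.8% | 12.25% | 9.4% | 11.75% |
| 2 | 11.6% | 14.5% | 10.8% | 13.5% |

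The full span is 6.2% to 14.5%. At the midpoint (R = 60%, p = 9%), k = 0.5, 1.5 and 2 give 7.2%, 10.8% and 12.6%.

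At k = 0.5 or 1.5 the shift is 1.4–2.25 points: more than twice the simple half-width but below the clustered one. At k = 2 it is 2.8–4.5 points, above the clustered half-width in all four columns. At the midpoint the two are equal when 0.4 × (k − 1) × 9 = 2.9, which gives k of about 1.8.

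**4. The same question by response rates.** Let r be the response rate of abused women divided by that of other women (assumed), and P the true prevalence. Then observed = P·r / (P·r + 1 − P).

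| r | True 8% | True 10% |
|---|---|---|
| 0.6 | 4.96% | 6.25% |
| 0.8 | 6.50% | 8.16% |
| 1.2 | 9.45% | 11.76% |

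The errors run from −3.75 to +1.76 points, so the size is similar by either route and both signs are possible.

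**5. The check by arm.** For any characteristic, the difference between arms among responders equals the difference between arms among all births, plus the difference between arms in responder selection. The planned comparison by arm observes only the sum. With four teams per arm, chance differences among births can be appreciable. A benchmark for each arm is needed to separate the two terms, and a single regional benchmark does not supply one.

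**The case against.** The strongest reply is that much of this is silence in a condensed article. Nowhere does it say that prevalence will be unweighted, and weighting may be specified in a full protocol or analysis plan that is not shown. That is right, so a reader who inferred a commitment to a crude estimate would go beyond the text. What remains rests on what is written: a safeguard is named, it is descriptive, and adjustment is limited to primary outcomes.

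A reader might also infer that nothing is checked by arm. The article does not support that. It compares survey women's characteristics by arm, which would reveal some differential response even though the stated purpose is randomisation balance. Nor does it say that the regional data will be pooled rather than split by area; it simply promises no split.

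The trial comparison is better protected than prevalence. Primary outcomes are adjusted for abuse status and socio-economic status. Survey disclosure and referral are reported among women reporting IPV, so a lower response from abused women does not by itself bias them. Inquiry, safety plans and referrals also come from routine nurse data, which survey non-response does not touch.

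A further inference, that prevalence must be understated, is also unsupported. The booklet is presented as a survey on health care with a new baby, with partner questions in one of seven sections, and the article gives no evidence on direction.

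Finally, the fix has limits. Prevalence is a secondary outcome, and reminders are planned, although the expected response already allows for a reminder. The perinatal data cover all births in a year, whereas the survey covers clients who gave birth over eight months. Area-level tabulations may not be available. These points argue for modest wording and a fix that depends on the data, but they do not remove the gap.

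**Conclusion.** The point holds in a limited form. Aim 3 claims accuracy, 35–45% non-response is expected, and the stated comparison with regional perinatal data is not linked to any prevalence estimate. Following the text as written leaves prevalence uncorrected.

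With k between 0.5 and 2, an observed 8–10% is compatible with about 6–15%. The shift reaches the clustered half-width of about 2.9 points only towards the upper end of that range (k of about 1.8 or more at the midpoint). This rests on an assumed k of unknown direction and on applying the stated intra-cluster correlation of 0.02 to prevalence.

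For the survey-based primary outcomes the finding is narrower. The planned comparison by arm cannot separate chance imbalance from differential response, but no bias in those outcomes has been shown. The change is worth making and cheap, and it does not call the trial design into question.

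**What to change.** - Report prevalence weighted by post-stratification or raking to the perinatal data already planned, using characteristics held in both sources and working by LGA where the data allow. Show the unweighted figure beside it, with cluster-based intervals for both.
- Report response fractions, and comparisons of responders with births, by arm and by LGA. Mailing and return counts should be obtainable from the company that sends and receives the surveys.
- Repeat the survey-based primary comparisons with the weights as a sensitivity analysis.
- Qualify the word accurate in Aim 3, because weighting removes only the part of non-response explained by the weighting variables and not the part driven by abuse itself. A table over a range of k, as above, would show readers what remains.
- State how the perinatal benchmark differs from the survey population in period and coverage.

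The cost is slightly wider intervals and a little more analysis, with no new data collection from women. If LGA-level perinatal tables cannot be obtained, weight at the finest level available and say so.

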#### Recruitment of clusters: MCH nurse teams in north west Melbourne

Team leaders of eight MCH teams, located in eight local government areas were invited to participate in a previous study MOSAIC [26] and all agreed. Each team leader and their manager signed a supplementary letter to the original Memorandum of Understanding to participate in this subsequent study.

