#### Randomization

The randomization of nurse teams at that time occurred at a public randomization meeting. Names of the MCHN teams, stratified by numbers of births per local government area and paired in size, were concealed in opaque envelopes and the random selection made by an invited guest from outside the project or research team. MCH Team Leaders were present to ensure the fairness of the process and to check the contents of the envelopes prior to their being sealed. For MOVE, all eight teams agreed to the reverse of the previous randomisation allocation, so that teams allocated to comparison status in MOSAIC formed the intervention arm for MOVE and those previously allocated intervention status formed the comparison arm.

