#### Intervention development phase – toward a model of sustainable good practice

This phase involved three strategies:

1.We conducted Participatory Action Research (PAR) with four volunteer MCHN consultants (one from each of four intervention MCHN teams) who explored the barriers and sought answers to these problems within their teams. PAR has been defined as ‘collective, self reflective inquiry that researchers and participants undertake, so they can understand and improve upon the practices in which they participate and the situations in which they find themselves’ [38]. Over a six-month period, at regular monthly meetings with MOVE staff, questions derived from earlier feedback in MOSAIC [26], discussion about barriers and enablers of IPV screening practices, and informed by the NPT framework [36] were agreed and nurse consultants took them away to their teams for discussion and feedback. The two groups (nurse consultants and MOVE staff) met over a six month period to discuss team feedback and reach agreement on the major aspects of a good practice model to be outlined in clinical pathways and guidelines. All meetings were recorded on tape and notes derived from them informed further discussion. We also drew on a GP systems intervention then being piloted in the UK (IRIS [23]) for strategies to strengthen links between clinicians and family violence services.

2. A systematic review of interventions (with controlled or comparison designs), guidelines or protocols targeted at improving the response of health care practitioners (HCPs) working with women experiencing IPV, their children and partners using abusive behaviors was conducted using Medline, Cochrane and Campbell Collaboration databases and CINAHL. Further details of the search terms and inclusion/exclusion criteria are available from the authors. Results were synthesized and presented to the nurse consultant and research group and the advisory group of key stakeholders.

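### Robust standard errors from only eight clusters, with no small-sample correction named, understate uncertainty in the survey-based primary comparisons

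*Protocol article*

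**What the plan says.** The protocol article, under Data analysis and reporting (Women's survey), states that "variance estimates in models will be adjusted for the effect of the clustered (LGA) selection of participants". It assigns contingency tables to bivariate analyses and "binary logistic regression with robust standard errors for multivariate models". Primary outcomes are to be analysed stratified by and adjusted for abuse status and for potential confounders, including socio-economic status.

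The number of clusters comes from the section on recruitment of clusters: "Team leaders of eight MCH teams, located in eight local government areas". The section on the intervention development phase describes nurse consultants as "one from each of four intervention MCHN teams", so the comparison is four teams against four. Under Randomization, the teams were "stratified by numbers of births per local government area and paired in size". The pairs are not mentioned in the analysis section.

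Under Survey sample size calculation, the article states "We adjusted for an intra-cluster correlation of 0.02 from a previous IPV primary care study". No alpha, reference distribution, degrees of freedom or finite-sample correction is given.

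**The concern.** The sandwich variance is consistent as the number of clusters grows. The number of women does not help: 10,000 mailed questionnaires still leave eight independent units, and 8 − 2 = 6 degrees of freedom for the arm comparison. Two faults act in the same direction. The uncorrected estimator is biased downward when clusters are few, and a normal reference ignores how poorly the variance is estimated from eight teams.

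P-values would then be too small and confidence intervals too narrow wherever the regression is used for the survey outcomes on inquiry, disclosure and referral. Ordinary variation between nurse teams could be read as an effect of the enhanced screening model, in a trial meant to inform screening policy.

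**Working it through.** **Inputs from the article.** Eight clusters, 4 v 4; intra-cluster correlation 0.02; 5,000 women mailed per arm; response 55-65%; abuse in the previous 12 months 8-10%. At 60% response this is 5,000 × 0.60 / 4 = 750 respondents per team. At 9% abused, it is 750 × 0.09 ≈ 67 abused respondents per team.

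**Assumptions.** Two-sided 5% test; team sizes; no outcome variation shared within size pairs, unless stated otherwise. The article gives no type I error figure to reproduce.

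**Step 1. Bias, equal teams, no covariates.** Let SS be the sum of squared deviations of the four team proportions in one arm from their mean.
- The uncorrected sandwich variance of the arm mean is SS/16.
- The unbiased variance is [SS/3]/4 = SS/12.
- The ratio is 12/16 = 3/4. With the usual factor G/(G−1) = 8/7 it becomes 3/4 × 8/7 = 6/7.

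**Step 2. Type I error, equal teams.** The correctly scaled statistic follows t on 6 df to a good approximation, so the true error is P(|t6| > c × √ratio), where c is the critical value used.

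| Variance | Reference | Effective cut-off | Type I error |
|---|---|---|---|
| Plain sandwich | normal | 1.960 × √0.75 = 1.697 | 14.1% |
| With 8/7 | normal | 1.960 × √(6/7) = 1.815 | 12.0% |
| With 8/7 | t, 7 df | 2.365 × √(6/7) = 2.189 | 7.1% |
| With 8/7 | t, 6 df | 2.447 × √(6/7) = 2.265 | 6.4% |
| Unbiased | t, 6 df | 2.447 | 5.0% |

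**Step 3. Unequal teams.** Beta-binomial data were simulated under the null with intra-cluster correlation 0.02 and allocation within size pairs (40,000 runs per setting, no covariates). The unequal sizes are assumed: pairs at 0.5, 0.8, 1.1 and 1.6 times the mean, a 3.2-fold range.

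| Setting | Plain, normal | 8/7, normal | 8/7, t(7) | Team-level t(6) |
|---|---|---|---|---|
| All women, mean 750, equal | 14.0% | 11.8% | 6.9% | 5.0% |
| All women, mean 750, unequal | 17.7% | 15.4% | 10.0% | 5.4% |
| Abused women, mean 67, equal | 14.2% | 12.1% | 7.1% | 5.0% |
| Abused women, mean 67, unequal | 17.0% | 14.7% | 9.1% | 5.0% |

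Smaller separate simulations (2,500 runs) with one or two covariates gave similar results; for moderately unequal teams with a normal reference the range was 14.6-19.3%. A stronger assumed spread (0.3 to 2.1 times the mean) gave about 19-23%.

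**Step 4. Interval width, equal teams.** Ratio of the correct 95% half-width to the half-width used:
- plain sandwich, normal: 2.447/1.697 = 1.44;
- 8/7, normal: 2.447/1.815 = 1.35;
- 8/7, t(7): 2.447/2.189 = 1.12.

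**Step 5. If the pairs are informative.** Equal teams, with a share of the between-team variance common to each pair:

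| Shared variance | Robust, normal (8/7 to plain) | Unpaired t(6) |
|---|---|---|
| 0% | 12-14% | 5.0% |
| 30% | about 7.5-9.1% | 2.8% |
| 50% | about 4.9-6.0% | 1.7% |

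**Step 6. Permutation within pairs.** Four pairs give 2⁴ = 16 allocations, so the smallest two-sided p-value is 2/16 = 0.125.

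**The case against.** The strongest reply is that the article does not state a normal reference. It names robust standard errors and stops there. A bias-corrected sandwich is still a robust standard error, and the correction and degrees of freedom may stand in an analysis plan that is not shown. This stands in part: the 12-18% range is conditional on the normal reference. It does not dispose of the point, because the article names an estimator that performs badly with eight clusters, and the common 8/7 factor with t(7) still leaves about 7-10%.

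Two further replies stand as limits. Team sizes are not given, so every unequal-team figure rests on an assumed spread. Pairing by births could also reduce the inflation if it explains outcome variation. The article neither shows nor excludes this, and in that case the unpaired t(6) test is conservative.

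A reader might infer more than the document supports:
- That the trial's type I error simply is 12-18%. It is not fixed by the document, for the reasons just given.
- That every survey primary outcome is affected without exception. The article does not call the regression the sole primary analysis; it also plans contingency tables and differences in proportions, with routine data alongside.
- That eight clusters cannot support more than about seven parameters, so the adjusted models fail. That is a rank limit on the covariance matrix and bears on joint tests. The arm coefficient still has a computable standard error. It remains a reason to keep the covariate list short.

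**Conclusion.** The point holds in conditional form. The planned variance method is unsuitable for four clusters per arm unless a small-sample correction and cluster-based degrees of freedom are added, and the article names neither. Under the stated assumptions, the type I error is about 12-14% (equal teams) or 14-18% (moderately unequal teams) with a normal reference, and about 7-10% with the 8/7 factor and t(7). With equal teams, correct intervals are about 35-44% wider than normal-based robust intervals and about 12% wider than those using 8/7 with t(7). Informative pairs would shrink the problem; more strongly unequal teams would enlarge it. It is worth settling before analysis because it concerns the error rate of the survey comparisons and is cheap to correct.

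**What to change.** For the survey-based primary outcomes, specify one of the following:

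1. A comparison of the eight team proportions by t-test on 6 df. For covariate adjustment, use the two-stage method: an individual-level logistic model without the arm term, then a t-test on the team-level residuals.
2. The planned logistic model with a bias-corrected sandwich variance (for example Kauermann-Carroll or Fay-Graubard) and t on 6 df. With equal teams and no covariates each team has leverage 1/4, so the Kauermann-Carroll correction multiplies the variance by 1/(1 − 1/4) = 4/3, which removes the 3/4 bias.

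Under either option, state the reference distribution and degrees of freedom, and keep the number of adjustment covariates small. Do not rely on a permutation test within the four pairs, since it cannot reach p < 0.125.

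The cost is a few sentences of analysis wording and a few lines of code, with no change to conduct or data collection. Intervals will be wider. The unweighted team-level test loses some efficiency if team sizes differ, and an unpaired t(6) test is conservative if the pairs share outcome variation.
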